##### Power analyses

Optimal Design software [43] was used to assess statistical power. As previously stated, covariates will be included in all models to help improve power to detect a treatment effect [35, 36]. Power will be computed on a modest effect size estimate of .30. With a minimum final sample size of 108 participants and explaining 40% of the variance in the outcome, we have .51 power to detect an effect size of .30. However, power increases to .80 if 50% of the outcome variance is explained by covariates. If 60% of the outcome variance is explained via covariates, we have greater than .80 power to detect an effect size of .20. We believe that an effect size of .30 is attainable and we also expect that baseline values of the dependent variable of interest as well as other baseline variables are likely to account for 50% of the variance in the dependent variable. While we recognize that power will be more limited for the exploratory questions addressed (and will supplement all analyses with the use of effect sizes), we do feel that the knowledge gleaned will provide useful information with regard to dissemination of the simulation training — addressing whether implementation via telehealth is statistically equivalent to in-person implementation as well as providing preliminary knowledge about the amount and predictors of change over time.

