### Design

The study is a randomized controlled trial with an experimental group and a control group allocated with a 1:1 randomization ratio. All trainees are randomized to control and experimental learning groups using Wei’s urn randomization [23] which provides overall balance at the end of accrual but also gives good, often near-perfect, balance within many strata [24, 25]. Randomization strata include medical learner groups (i.e., medical residents, pediatric residents, and nurse practitioners) and gender. After all baseline measures are completed, participants are randomized to experimental condition by the project statistician, who remains blinded to study condition.

Participants in both groups complete a 48-min, 6-module, online video-based training on suicide prevention (Commitment to Living for Primary Care; CTL-PC). Upon completion of the online teaching program, participants in the experimental group engage in two standardized patient practice interactions over the course of 4 to 6 months. One practice interaction takes place in-person and the other uses a telehealth model. The order is randomized. Then, approximately 6 to 8 months (depending on schedules, see below) after video-based learning, both control and experimental groups engage in an in-person “test case” standardized patient interaction.

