### Participants

Participants are second year trainees from two education programs at the University of Rochester Medical Center: the nurse practitioner training program (NP) and medical residency programs, which included second year residents from pediatrics, the combined internal medicine-pediatrics program, and family medicine. These learner groups were chosen because most are preparing for careers in primary care. The training directors of the programs agreed to incorporate suicide prevention training into their curriculum for the duration of the grant and to support randomization of learners. As a result, all trainees receive the training according to their randomized condition. Trainees engage in a consent process (conducted by study personnel) for analysis of their data; those who do not consent for the study receive the training but their data are not analyzed. All trainee participants are fully informed that the SP interactions are part of their suicide prevention training. We collect non-identifiable demographic data at baseline for all trainees in order to compare those who enrolled in the study and those who did not. We plan to enroll 108 participants generally divided between residents and NPs.

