### Statistical analysis

#### Data processing

Data collection and storage is managed by REDCap, a secure software system supported by the institution. (Data management procedures are fully described in the study manual.) A baseline check of randomness will be conducted for each demographic and outcome variable collected. Because we are interested in establishing equivalence (as opposed to detecting differences), a more conservative alpha level will be applied (α = .20). Categorical variables will be analyzed using chi-square tests; continuous variable differences will be assessed using a general linear model approach (ANOVA). Any baseline difference will be controlled for statistically in all subsequent analyses. For analyses related to hypotheses, α = .05 and covariates will include stratification variables of gender and residency/NP training program, race/ethnicity, age, and the specific outcome baseline score as well as any other variables found to differ at baseline. Effect sizes (Hedge’s *g*) will also be examined for each of the study hypotheses.

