##### Missing data

While we will make every effort to collect all data at each data collection point, missing data is likely. For analyses examining mean differences, pairwise deletion of missing data will be used, thus retaining all available information. As a form of sensitivity analyses, however, multiple imputation of missing data will be conducted. In short, multiple imputation uses a regression based approach to impute values for data that are missing. So that variance is not artificially constrained, multiple imputation incorporates random error into the imputation process [44, 45]. To improve estimates, the procedures put forth by Allison [46] regarding intervention studies will be followed. Here, each intervention condition is imputed separately and then the resulting datasets are merged. Following Rubin, [47] 10 imputations will be performed and each of the 10 resulting datasets will be analyzed as above. The results obtained from the 10 datasets will be combined following Rubin [47]. Multiple imputation has consistently demonstrated less biased estimates than most other traditional approaches to the handling of missing data (i.e., listwise, pairwise, mean imputation, single regression imputation) [44, 45, 48].

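### Two of the three stated power figures do not follow from 108 participants: .80 should be .59, and greater than .80 should be .37

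*Protocol article*

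**What the plan says.** The Power analyses section of the protocol article reports three scenarios, calculated with Optimal Design software:

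- Effect .30, 40% of outcome variance explained by covariates: power .51. The sample is introduced as "With a minimum final sample size of 108 participants and explaining 40% of the variance in the outcome".
- Effect .30, 50% explained: "However, power increases to .80 if 50% of the outcome variance is explained by covariates".
- Effect .20, 60% explained: "If 60% of the outcome variance is explained via covariates, we have greater than .80 power to detect an effect size of .20".

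The section then adopts the second scenario as its expectation. It regards an effect of .30 as attainable and 50% explained variance as likely.

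On sample size, the Participants section says "We plan to enroll 108 participants generally divided between residents and NPs", and the Missing data section says that "missing data is likely".

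**The concern.** The three figures do not fit together. Raising the explained variance from 40% to 50% shrinks the residual standard deviation only slightly, which cannot lift power from .51 to .80. Cutting the effect by a third, from .30 to .20, while explaining a further 10% of the variance must lower power, yet the text still puts it above .80.

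The middle figure is the one the plan relies on, so it is in effect the trial's power claim. If it is too high, a non-significant primary result would be read against a power for an effect of .30 that the design does not have.

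A smaller point concerns the base of the calculation. All three figures assume 108 participants in the final analysis, but 108 is also the number to be enrolled, which leaves no room for loss.

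**Working it through.** **Inputs**

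- N = 108 in total, from Power analyses ("With a minimum final sample size of 108 participants").
- Equal arms of 54, from Design ("allocated with a 1:1 randomization ratio").
- Alpha .05, from Data processing ("For analyses related to hypotheses, α = .05").
- ANCOVA on individually randomised participants, from Hypothesis 3.
- Effect size d and explained variance R², from Power analyses.
- Two-sided testing, and an effect standardised on the unadjusted standard deviation. These are assumptions, because the article states neither.

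**Formula**

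For a 1:1 two-arm ANCOVA the noncentrality is ncp = d × √(N/4) / √(1 − R²). Power comes from the noncentral t distribution with N − 3 = 105 degrees of freedom and a critical value of 1.983. With N = 108, √(108/4) = √27 = 5.196.

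**The plan's own figure first**

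d = .30, R² = .40: ncp = .30 × 5.196 / √.60 = 1.559 / .775 = 2.012, power **.514**. The plan states .51, so this reproduces and identifies the likely method.

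**The other two by the same method**

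- d = .30, R² = .50: ncp = 1.559 / .707 = 2.205, power **.589**. The plan states .80.
- d = .20, R² = .60: ncp = 1.039 / .632 = 1.643, power **.370**. The plan states greater than .80.

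Spending four more degrees of freedom on covariates changes these by less than .001.

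**Internal consistency, without computing power**

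- From the first to the second scenario, ncp rises by the factor √(.60/.50) = 1.095, about 10%.
- From the second to the third, ncp changes by the factor (.20/.30) × √(.50/.40) = .745, a fall of about 25%.
- The third ncp (1.643) is also below the first (2.012), so the third scenario must have less power than the one the article puts at .51.

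**Could another reading give the stated values?**

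| Reading | d=.30, R²=.40 | d=.30, R²=.50 | d=.20, R²=.60 |
|---|---|---|---|
| Stated | .51 | .80 | >.80 |
| Two-sided .05, 108 in total | .51 | .59 | .37 |
| One-sided .05 | .64 | .71 | .50 |
| Two-sided alpha .20 | .77 | .82 | .64 |
| 108 per arm | .81 | .87 | .64 |
| SD multiplied by (1 − R²) | .74 | .88 | .74 |
| Percentage read as a correlation | .39 | .43 | .25 |
| Effect read as Cohen's f | .98 | .99 | .91 |

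No row gives all three stated values. Every row that lifts the second or third to .80 loses the .51.

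**What 80% power would need**

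- At N = 108: R² of about .70 for d = .30, or about .865 for d = .20.
- At the stated R²: N of about 176 for d = .30, R² = .50 (176 gives .799 and 178 gives .804), and about 316 for d = .20, R² = .60.
- At N = 108 and R² = .50: a detectable effect of about .385.

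**If fewer than 108 are analysed**

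The article gives no loss rate, so 10% and 20% are illustrations. For d = .30 and R² = .50, 97 analysed gives power .54 and 86 gives .49.

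**The case against.** The arithmetic has no real defence, but four points against the wider concern deserve a hearing.

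1. *The method is inferred.* Sidedness and the definition of the effect size are not stated, and one matching figure is good evidence rather than proof. This stands as a caveat. It does not change the conclusion, because one-sided testing still gives only .71 and .50.
2. *The enrolment point is separate and thinly supported.* The remark about missing data covers every collection point and is not specific to the 6-month test case. The training is embedded in the curriculum, which should limit loss, and multiple imputation is planned as a sensitivity analysis. It is fair to treat this as secondary. The mismatch between 108 enrolled and 108 as a minimum final sample remains.
3. *Readers are not wholly misled.* The article openly reports .51 at 40% explained variance and commits to effect sizes alongside tests. How a null result would be reported is therefore a risk, not a certainty. The power under the expected scenario is still misstated.
4. *Correcting the numbers leaves the 50% itself doubtful.* Power analyses justifies it partly by baseline values of the outcome. The covariates listed under Hypothesis 3 are gender, training program, race/ethnicity and age, and no standardized patient interaction before training is described. So .59 may itself be generous for the primary outcome. This strengthens the case for correction.

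**Conclusion.** The concern holds. With 108 analysed, equal arms and two-sided alpha .05, power is .59 rather than .80 for an effect of .30 with 50% explained, an overstatement of 21 points. It is .37 rather than above .80 for an effect of .20 with 60% explained, an overstatement of at least 43 points. In the scenario the plan expects, the chance of missing the planned effect is 1 − .59 = .41, about 4 in 10.

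The exact values rest on two-sided testing and on an effect standardised by the unadjusted standard deviation, the combination that reproduces the plan's own .51. That the stated figures are wrong does not depend on those assumptions: they contradict one another, and none of the alternative readings tried produces all three. The values are upper limits if fewer than 108 are analysed.

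**What to change.** Rewrite the Power analyses paragraph:

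- State that the calculation is two-sided at .05 with 108 participants in total. If the software run used other settings, state those and recompute all three figures with them.
- For an effect of .30, give power .51 at 40% explained and .59 at 50%. For an effect of .20, give .37 at 60%.
- Give the effect detectable with 80% power, about .385 at 50% explained.
- Say whether 108 is the number enrolled or the number analysed. Repeat the figures at the number expected to be analysed; for example, at .30 and 50% explained, .54 with 97 and .49 with 86.
- For the skills outcome, say which covariates are expected to explain 50% of the variance, or show power at a lower value too.

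The cost is one reworded paragraph and a less favourable power statement. The design, tests and enrolment do not change.

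### Two of the three stated power figures are wrong: with 108 participants, power is about .59 (not .80) for an effect of .30 with 50% explained variance, and about .37 (not above .80) for .20 with 60%

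*Protocol article*

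**What the plan says.** All three figures are in the Power analyses section of the protocol article, which sets the base case as follows: "Power will be computed on a modest effect size estimate of .30".

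- **Scenario 1.** "With a minimum final sample size of 108 participants and explaining 40% of the variance in the outcome", the article reports that "we have .51 power to detect an effect size of .30".
- **Scenario 2.** For the same effect, "power increases to .80 if 50% of the outcome variance is explained by covariates".
- **Scenario 3.** "If 60% of the outcome variance is explained via covariates, we have greater than .80 power to detect an effect size of .20".

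The section then says that the authors regard an effect of .30 as attainable and expect baseline variables to explain half of the outcome variance. Scenario 2 is therefore the one on which the sample size is defended.

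The other inputs are in the Design section ("an experimental group and a control group allocated with a 1:1 randomization ratio") and the Data processing section ("For analyses related to hypotheses, α = .05 and covariates will include stratification variables"). The article does not say whether the test is one- or two-sided.

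**The concern.** Covariates raise power by shrinking the residual standard deviation, which is proportional to sqrt(1 − R²). Going from 40% to 50% explained variance shrinks it by less than a tenth, too little to lift power from .51 to .80. Scenario 3 looks worse still: the effect is cut by a third, explained variance rises only to 60%, and yet the stated power exceeds that of both other scenarios.

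At stake is the only quantitative case for the sample size. If scenario 2 is wrong, the trial is much less likely to detect the effect it expects than its readers are told. If scenario 3 is wrong, the article claims a sensitivity to small effects that the design lacks, and a reader could take a non-significant result as evidence against an effect of .20.

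**Working it through.** **Inputs.** Total N = 108 (Power analyses). Allocation 1:1, so 54 per arm (Design). Alpha .05 (Data processing). Effect sizes .30 and .20 and explained variances (R²) of 40%, 50% and 60% (Power analyses). Two-sided testing is assumed and is checked in step 1.

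**Formula.** For a two-arm ANCOVA with effect d in units of the unadjusted SD, the noncentrality is

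ncp = d / sqrt[(4/N)(1 − R²)].

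Power comes from the noncentral t distribution. Allowing for 0 to 10 covariates in the degrees of freedom changes power by less than .001.

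**Step 1: reproduce the plan's first figure.** d = .30, R² = .40:

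ncp = .30 / sqrt(.03704 × .60) = .30 / .1491 = 2.012, power **.51**.

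This matches the stated .51, and so supports the reading used here: 108 in total, two-sided .05, R² as the proportion of variance explained.

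**Step 2: apply the same method to the other two.**

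| Scenario | d | R² | SE | ncp | Power | Stated |
|---|---|---|---|---|---|---|
| 1 | .30 | .40 | .1491 | 2.012 | .51 | .51 |
| 2 | .30 | .50 | .1361 | 2.205 | .59 | .80 |
| 3 | .20 | .60 | .1217 | 1.643 | .37 | > .80 |

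**Step 3: check consistency without using N or alpha.** With N, alpha and sidedness held common, power rises with d / sqrt(1 − R²):

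- Scenario 1: .30 / sqrt(.6) = .387
- Scenario 2: .30 / sqrt(.5) = .424
- Scenario 3: .20 / sqrt(.4) = .316

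Scenario 3 has the smallest value. Its noncentrality is .316/.387 = .816 of scenario 1's, so its power must be below that of scenario 1, whatever the common settings. From scenario 1 to scenario 2 the noncentrality rises by sqrt(.6/.5) = 1.095. Going from .51 to .80 at two-sided .05 needs an ncp of about 2.83 against about 2.00, a factor of 1.41.

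**Step 4: try other readings.** Power in the order of scenarios 1, 2 and 3:

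| Reading | 1 | 2 | 3 |
|---|---|---|---|
| Stated | .51 | .80 | > .80 |
| One-sided .05 | .64 | .71 | .49 |
| 108 per arm | .81 | .87 | .64 |
| Alpha .20, two-sided | .77 | .82 | .64 |
| R² read as a correlation | .40 | .44 | .25 |
| One-sided .05, R² read as a correlation | .52 | .56 | .36 |
| SD scaled by (1 − R²) | .74 | .88 | .74 |
| Effect size read as Cohen's f | .98 | .99 | .91 |

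None yields the three stated figures together. The one alternative that comes near .51 for scenario 1 leaves the other two far short.

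**Step 5: what 108 participants can deliver** (two-sided .05).

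| R² | Power, d = .30 | Power, d = .20 | Effect detectable with .80 power |
|---|---|---|---|
| .40 | .51 | .26 | .42 SD |
| .50 | .59 | .31 | .38 SD |
| .60 | .68 | .37 | .34 SD |

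Power of .80 would need R² of about .70 for an effect of .30 and about .86 for .20. At R² = .50 the half-width of the 95% confidence interval is about 1.98 × .1361 = .27 SD.

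**The case against.** The arithmetic is hard to dispute, and no reading of the inputs rescues the two figures. What can be said for the article concerns consequence and remedy.

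- **The article does not hide weak power.** It reports .51 at 40% explained variance. That is true, but it goes on to say that 50% is what it expects and gives .80 for that case, so the reader is steered away from the weak figure.
- **Nothing says a null primary result will be read as excluding small effects.** The article commits to effect sizes for every hypothesis, and where it wants to conclude equivalence it uses a separate procedure with a preset margin. This stands: misreading a null result is a risk the wrong figure creates, not something the plan announces. A rule for interpreting a non-significant result is therefore a useful addition, not part of the correction.
- **Sidedness is not stated.** Two-sided testing is inferred from the match to .51 and should be labelled as an assumption. One-sided testing loses that match and still falls short in both other scenarios.
- **The 50% may not apply to the primary outcome.** The article counts partly on baseline values of the outcome to reach it. The Hypothesis 3 section lists only gender, program, race/ethnicity and age for observed skills, and under Procedures controls have no standardized patient interaction before the test case. The .59 should therefore be given as conditional on 50%. This makes the position weaker, not stronger.
- **Attrition.** The Power analyses section treats 108 as the minimum final sample, whereas the Participants section plans to enroll 108. The calculation takes 108 analysed participants at face value and does not depend on how that is resolved.

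**Conclusion.** The concern holds. Two of the three power figures are wrong: .80 should be about .59, and more than .80 should be about .37. Under the assumptions the article itself adopts (effect .30, 50% explained variance), the chance of missing a true effect is about 41%.

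The replacement values assume 108 analysed participants split equally, a two-sided .05 test, R² as the proportion of variance explained, and no multiplicity adjustment. The finding that scenario 3 cannot have more power than scenario 1 needs none of the specific values for N, alpha or sidedness, only that they are common to the scenarios. Because the sample size is defended on scenario 2, the error must be corrected.

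**What to change.** In the Power analyses section, replace the second and third power statements with wording along these lines: *Assuming a two-sided test at .05 and 108 analysed participants allocated 1:1, power to detect an effect of .30 is .59 if covariates explain 50% of the outcome variance, and power to detect an effect of .20 is .37 if they explain 60%. With 50% explained, the effect detectable with .80 power is about .38 SD.*

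Remove the claim of more than .80 power for an effect of .20. Revise the sentence that relies on the 50% case so that it no longer implies .80 power, and say that 50% is an assumption for the primary skills outcome.

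A further sentence is worth adding, though the correction does not depend on it: a non-significant primary result will be interpreted from its confidence interval and not as evidence that simulation adds nothing.

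The cost is one reworded paragraph and a less favourable stated power. No participants, procedures or analyses change.

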### Procedures

Following enrollment, participants receive an email with instruction to complete online baseline assessments and view the teaching videos within 14 days. All surveys are completed online using the same secure website that hosts the CTL-PC videos. After they have viewed the videos, participants in the experimental condition engage in two practice SP interactions over a period of about four months, with at least one month between interactions. Participants in the control condition do not have practice interactions. At approximately six months following completion of online teaching, both experimental and control participants complete the same face-to-face SP test case. There are two SP character scenarios for the experimental practice sessions and one test case SP scenario.

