The primary hypothesis of the study is that participants in the experimental condition will demonstrate significantly better skills compared to the control group, as measured by reliable, observed ratings of behaviors in the SP assessment at 6 months. We will use ANCOVA to assess SP training effects at follow up on all participants’ skills. Skills will be measured by reliable observational ratings of several suicide specific and general interviewing skills. In all instances, gender, training program group, race/ethnicity, and age will be included as covariates to aid in statistical power [35, 36].

##### Exploratory analysis for hypothesis 3

We will examine statistical equivalence between the two SP modalities (face-to-face; telehealth). Similar to Hypothesis 1 (above), Tryon’s inferential confidence intervals will be used to assess for equivalency among face-to-face and telehealth modalities [31, 32]. Following Treadwell and colleagues [33], a standardized small effect of .20 [34] will define the criterion for establishing a MID. As a form of sensitivity, a MID of .10 will also be examined. As a second form of sensitivity, multilevel modeling will be used to decompose the variance associated with these observed training outcomes into variance attributed to the person as well as variance attributed to time (first SP interaction, second SP interaction) and variance attributed to modality. Since the order is randomized, we might expect more variance attributed to time (improving over time). Within these models, the learner (person) defines level 2 with the observed ratings being the dependent level one variables. Both time and modality will be entered as time varying covariates.

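### The power case for the primary outcome leans on a baseline skill score that the design never collects, and two of its three power figures do not reproduce even on their own assumptions

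*Protocol article*

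**What the plan says.** The protocol article makes these statements about the primary comparison.

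- **Power analyses.** For 108 participants, power is given as .51 for an effect of .30 with 40% of outcome variance explained, .80 for .30 with 50% explained, and above .80 for .20 with 60% explained. The 50% case is the one relied on, because "baseline values of the dependent variable of interest as well as other baseline variables are likely to account for 50% of the variance". No separate case is given for the primary outcome.
- **Hypothesis 3 (primary).** The outcome is rated skill in the SP assessment at 6 months, analysed by ANCOVA, where "gender, training program group, race/ethnicity, and age will be included as covariates to aid in statistical power". No baseline score is listed.
- **Data processing.** The covariates for hypothesis analyses also include "the specific outcome baseline score as well as any other variables found to differ at baseline". Differences at baseline are judged at α = .20.
- **Procedures.** The experimental arm's practice sessions follow the videos. "Participants in the control condition do not have practice interactions."
- **Measures.** Baseline surveys collect knowledge, self-efficacy, previous suicide prevention training, previous SP experience, and prior professional and personal experience with suicide.
- **Design.** "Randomization strata include medical learner groups (i.e., medical residents, pediatric residents, and nurse practitioners) and gender."

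**The concern.** A baseline value of the outcome is usually the strongest covariate in an ANCOVA, and the planning case names it as a source of the 50%. Skill, however, is rated only from recorded SP sessions. If none takes place before randomisation, the primary outcome has no such covariate, and the explained variance must come from whatever else is in the model. The model fixed for Hypothesis 3 contains four background variables.

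At stake is how the primary result is read. If the trial is described as having .80 power for .30 when its real power is well below that, a null finding may be taken as evidence that simulation adds nothing to online teaching. Baseline information that might sharpen the comparison, and that costs nothing more to obtain, is also left to a chance-driven entry rule.

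**Working it through.** **Step 1: is there a baseline for observed skill?** Design says that baseline measures are completed before randomisation. Procedures says that these are online surveys. The experimental arm's first SP session comes after randomisation and after the videos, and the control arm's only SP session is the test case. So neither arm has a pre-randomisation skill score. The baseline status in the growth-curve analysis is the first practice session, in the experimental arm only, and cannot serve as a covariate for the group comparison.

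**Step 2: inputs.** N = 108 (Power analyses). Arms are "allocated with a 1:1 randomization ratio", so 54 per arm. "For analyses related to hypotheses, α = .05". Sidedness is not stated in the power section, so two-sided is assumed. The effect d is taken in units of the unadjusted SD.

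**Step 3: formula.** With covariates explaining a share R² of the variance, the residual SD is √(1 − R²). The noncentrality is δ = d / √(1 − R²) × √(N/4), with √(108/4) = 5.196. Power comes from the noncentral t on 106 df.

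**Step 4: the plan's own figures.**

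| d | R² | δ | Power, noncentral t (normal) | Stated |
|---|---|---|---|---|
| .30 | .40 | .30/.775 × 5.196 = 2.01 | .51 (.52) | .51 |
| .30 | .50 | .30/.707 × 5.196 = 2.20 | .59 (.60) | .80 |
| .20 | .60 | .20/.632 × 5.196 = 1.64 | .37 (.38) | above .80 |

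The first figure reproduces, which supports the method. The other two do not. Other readings do not rescue them together:

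- One-sided .05 gives .64, .71 and .50.
- 108 per arm gives .81, .87 and .64.
- Two-sided .20 gives .77, .82 and .64.

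Power of .80 at d = .30 and N = 108 needs R² of about .70. At R² = .50 it needs 176 participants in total.

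**Step 5: power without a baseline score.** The documents give no R² for observed skill, so the range below is an assumption (d = .30, N = 108, two-sided .05).

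| R² | δ | Power | Effect detectable at 80% power |
|---|---|---|---|
| 0 | 1.56 | .34 | .54 SD |
| .10 | 1.64 | .37 | .52 SD |
| .20 | 1.74 | .41 | .49 SD |
| .30 | 1.86 | .45 | .46 SD |

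**Step 6: cost of more covariates.** At R² = .30, moving from 5 to 12 covariate degrees of freedom (106 − 5 = 101 to 106 − 12 = 94 residual df) changes power from .4545 to .4540. The loss through the critical value is below .001.

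**The case against.** Five points can be made for the plan.

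- **The collected measures are not shut out.** A reader might infer that baseline knowledge, self-efficacy and prior experience are excluded from the primary model. They are not: Data processing admits any variable that differs at baseline. With five independent checks at .20, the chance that at least one enters is 1 − .8⁵ = .67. This stands as a correction, but the rule selects on chance imbalance rather than on prognosis, so it is no substitute for a prespecified list.
- **The primary ANCOVA can be run as written.** Hypothesis 2 names a baseline of the dependent variable where one exists (self-efficacy), and Hypothesis 3 does not. The Data processing rule can be read as applying only where a baseline exists. Leaving out prognostic covariates does not bias a randomised comparison. All of this stands. The point concerns power and precision, not validity.
- **The power sentence also cites other baseline variables.** It does, and training program may be strongly prognostic, since residents and nurse practitioners are different learners. The documents quantify neither, and the 50% remains unsupported for observed skill.
- **The gain from adding covariates is small.** If R² rose from .10 to between .20 and .30, power would rise from .37 to between .41 and .45. This stands.
- **The residency/NP wording may be shorthand.** Data processing calls it a stratification variable, so a reader should not infer that a two-level covariate is definitely planned.

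**Conclusion.** The concern holds in two separate parts.

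First, the baseline-value argument for 50% explained variance, and the outcome baseline score listed in Data processing, cannot apply to Hypothesis 3. This follows from the schedule alone.

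Second, the stated power is wrong even if the R² values are granted: about .59 instead of .80, and about .37 instead of above .80. This rests on a two-sided .05 test, equal arms and an effect in unadjusted SD units. The same method returns the plan's own .51.

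It is tempting to blame the whole distance from .80 down to .34–.45 on the missing baseline. The figures do not support that. The step from .80 to .59 is a calculation error that affects any outcome. Only the step from .59 to .34–.45 comes from lower explained variance, and its size depends on the assumed R² of 0 to .30.

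Planned enrolment is also 108, equal to the stated minimum final sample, while the Missing data section calls missing data likely. Any loss would lower power further.

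**What to change.** 1. **Power analyses.** Correct the two figures: about .59 for d = .30 at R² = .50, and about .37 for d = .20 at R² = .60. State power for observed skill separately, without a baseline score and labelled as an assumption: R² 0 to .30, power .34 to .45, detectable effect .54 to .46 SD. Confine the baseline-value argument to self-efficacy, which has a baseline and is tested for a group difference. It does not suit knowledge, where the plan expects no group difference and assesses equivalence.
2. **Hypothesis 3 and Data processing.** Prespecify baseline knowledge, baseline self-efficacy, previous suicide prevention training, previous SP experience and prior experience with suicide as covariates in the primary ANCOVA, in place of entry by baseline significance test. State that the outcome baseline score applies only where one exists.
3. **Minor.** Say that learner group is coded at the three levels used as randomisation strata.

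The cost is plan wording and about 5 to 7 degrees of freedom, with no new data. The power lost through the critical value is negligible. Chance imbalance in the added covariates carries a small further cost, so they help only as far as they are prognostic. The documents do not quantify that gain. It is likely to be modest and will not bring power back to .80.
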